**Methods:**

A multicenter, randomized, parallel-group clinical trial will be conducted with a follow-up of 2 months. The scope of the study will be the primary care health centers of the Community of Madrid belonging to the Spanish public health system. The study population will be patients diagnosed with Parkinson disease, Alzheimer disease, and cardiovascular disease; their caregivers; and health professionals. The sample size will be 534 patients (380 in the intervention group). The intervention will consist of the use of the TeNDER system. The system will monitor the patients by means of biosensors, and their data will be integrated into the TeNDER app. With the information provided, the TeNDER system will generate health reports that can be consulted by patients, caregivers, and health professionals. Sociodemographic variables and technological affinity will be measured, as will views on the usability of and satisfaction with the TeNDER system. The dependent variable will be the mean difference in QoL score between the intervention and control groups at 2 months. To study the effectiveness of the TeNDER system in improving QoL in patients, an explanatory linear regression model will be constructed. All analyses will be performed with the 95% CI and robust estimators.

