### Sample Size

The European consortium that developed the proposal called for a sample size of 1766 patients (1031 in the control group and 735 in the intervention group) with the aim of using the TeNDER system to achieve an improvement in QoL, as measured by the Short Form–36 Health Survey (SF36) [23], of 6 points in the intervention group as compared to the control group.

According to previous studies, the SD for QoL score in the population with the chronic diseases under study (PD, AD, and CVD) ranges between 16 and 27 [23-25]. For the power calculation, we used the highest value of this SD. Therefore, the sample size will allow a power of 98.8% to detect ≥6 differences in the overall score of the SF36 questionnaire, if they exist. Calculations were performed with Epidat (version 4.2; Xunta de Galicia).

In the PCHC of the Madrid Health Service, as part of the European consortium, 534 patients will be included (380 in the intervention group and 254 in the control group). No differentiation by pathology will be established.

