#### Direct Data Collection

Once participants have agreed to participate in the study, they will be scheduled for the baseline visit (T0). At this visit, baseline and tool cocreation data will be collected. The final visit (T1) will take place 2 months after the intervention. Data collection during both visits will take place at the PCHC or at the patient’s home and will be carried out as face-to-face hetero-administered interviews by 2 project nurses. Data will be collected through questionnaires, and interviews will be indexed in an electronic data collection record (eDCR).

The primary outcome variable will be the QoL of patients measured using the SF36 questionnaire [23]. This is a 36-item questionnaire that includes 8 domains: physical functioning, role limitations due to physical problems, bodily pain, general health perceptions, mental health, role limitations due to emotional problems, social functioning, and vitality. Eight domain scores and a summary score (range 0-100) can be obtained; higher scores indicate better health-related QoL (HRQoL). In addition, six Likert-type questions are used to collect proxy indicators of QoL related to the TeNDER system. These questions are related to the perception of improved autonomy, support, improved self-care, and safety. In addition, we will collect sociodemographic variables such as sex, age, and nationality from patients, caregivers, and PCHPs. Also, technology affinity among the 3 types of users will be collected through a single ad hoc question. Clinical information collected from patients will include their main disease and other chronic diseases. The degree of autonomy and the need for help will be studied through ad hoc questionnaires at T0 and T1.

For a description of the usability of and satisfaction with TeNDER system after the intervention, the validated System Usability Scale questionnaire [24,25] will be administered to patients, caregivers, and PCHPs.

Caregivers’ QoL related to the care provided and the perceived satisfaction with the care provided will be studied through an ad hoc questionnaire.

The questionnaires (at T0 and T1) are included in Multimedia Appendix 1.

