### Data Analysis and Statistical Plan

A descriptive analysis of the characteristics of the participants will be performed with frequencies and percentages for qualitative variables and the mean (SD) or median (IQR) for the quantitative variables, according to their distribution. The mean difference in QoL score between the intervention and control groups will be studied with the corresponding 95% CIs at T1 (2 months). Differences in qualitative variables will be analyzed with the Pearson chi-squared test, and differences in normally distributed quantitative variables will be analyzed with the Student *t* test (2-tailed).

To study the effectiveness of the TeNDER System in improving QoL in patients, an explanatory linear regression model will be constructed. The dependent variable will be the mean difference in QoL score between the intervention and control groups at T1 (2 months). As patients will be recruited grouped by cluster (ie, PCHC), all the estimations will be performed with robust estimators. The analyses will be performed with Stata (version 14; StataCorp).

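### The effectiveness regression names the between-group mean difference as its dependent variable; the response should be each patient's T1 SF-36 score, with adjustment for the T0 score stated

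*Protocol article*

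**What the plan says.** The Data Analysis and Statistical Plan section promises that "an explanatory linear regression model will be constructed" to study effectiveness, and then: "The dependent variable will be the mean difference in QoL score between the intervention and control groups at T1 (2 months". The Methods part of the abstract has the same definition: "The dependent variable will be the mean difference in QoL score between the intervention and control groups at 2 months". No covariates are listed. The paragraph before the regression describes a comparison of mean QoL between arms at T1, with 95% confidence intervals and a two-tailed t test.

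Other sections define the outcome for the individual patient. Direct Data Collection says "The primary outcome variable will be the QoL of patients measured using the SF36 questionnaire", with a summary score from 0 to 100, and the Design section makes the patient the unit of randomization.

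On baseline, Direct Data Collection says of the T0 visit that "At this visit, baseline and tool cocreation data will be collected", and adds: "The questionnaires (at T0 and T1) are included in Multimedia Appendix 1". The Randomization section places allocation after the initial visit and says that it is done by pathology.

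**The concern.** A regression needs a response that takes a value for each unit analysed. The mean difference between arms is what such a regression returns, so the sentence puts the estimand where the outcome should be. As it appears in both the analysis section and the abstract, it is not a one-off slip.

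An analyst has to repair the sentence, and the text does not say how. Three repairs are plausible: the T1 score alone, the change from T0 to T1, or the T1 score adjusted for T0. They give different estimates and standard errors. The trial is unmasked, and its Discussion accepts that lack of masking may widen the difference between arms, so the primary model is better fixed in words than left to interpretation.

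The baseline score is also at stake. If it is available, it is probably a useful predictor of the T1 score, and a T1-only comparison does not use it.

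**Working it through.** **1. Can the stated model be fitted?** Write Y for a patient's T1 score and G for group (1 = intervention, 0 = control). In Y = a + b·G + error, b is the difference between arms. The protocol makes b the dependent variable. There is one b per trial, so there is nothing to regress. Y, the SF-36 score, is what Direct Data Collection names as the primary outcome.

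**2. Inputs for the size of the effect.**
- Target difference, Sample Size section: "of 6 points in the intervention group as compared to the control group".
- SD: stated range 16 to 27; the highest value was used for power (same section).
- Consortium arms: 735 intervention, 1031 control.
- Madrid arms: 380 intervention, 254 control. These sum to 634 against a stated total of 534, so alternatives are shown.
- Assumed: two-sided alpha 0.05 (not stated for the power calculation), correlation r of 0.3 to 0.7 between T0 and T1 (not given), no dropout, no clustering.

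**3. Formulas.** SE = SD × √k × √(1/n₁ + 1/n₂) and power = Φ(6/SE − 1.96). Here k = 1 for the T1 score alone, k = 2(1 − r) for the change score (equal SDs at T0 and T1), and k = 1 − r² for T1 adjusted for T0.

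**4. The plan's own figure.** For 735/1031 and SD 27, SE = 27 × √(1/735 + 1/1031) = 1.303, and power = Φ(4.60 − 1.96) = 99.6%. The plan states 98.8%, less than one point lower, so an unadjusted T1 comparison reproduces it closely.

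**5. Madrid, 380/254, SD 27.** Unadjusted SE = 27 × √(1/380 + 1/254) = 2.188, and power = Φ(2.742 − 1.96) = 78.3%. The three repairs compare as follows:

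| Assumed r | T1 alone | Change score | T1 adjusted for T0 | Adjusted SE |
|---|---|---|---|---|
| 0.3 | 78.3% | 64.0% | 82.0% | 2.09 |
| 0.5 | 78.3% | 78.3% | 88.6% | 1.90 |
| 0.7 | 78.3% | 94.3% | 97.0% | 1.56 |

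**6. Sensitivity.**

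| Arms (intervention/control), SD | T1 alone | Adjusted, r = 0.3 | r = 0.5 | r = 0.7 |
|---|---|---|---|---|
| 380/154, SD 27 | 64.3% | 68.4% | 76.6% | 90.3% |
| 280/254, SD 27 | 72.7% | 76.7% | 84.2% | 94.9% |
| 380/254, SD 16 | 99.6% | 99.8% | >99.9% | >99.9% |
| 380/154, SD 16 | 97.5% | 98.4% | 99.5% | >99.9% |
| 735/1031, SD 27 | 99.6% | 99.8% | >99.9% | >99.9% |

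The first two rows are two ways in which the Madrid total could be 534.

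**The case against.** The strongest reply is that this is a wording error with an obvious meaning. The primary outcome is the patient's SF-36 score, the patient is randomized, and the preceding paragraph reports the difference in means at T1. A sensible analyst would regress T1 scores on group and read off the coefficient. That is fair: the intended response is easy to recover. It does not settle whether T0 enters, and the sentence as printed still cannot be carried out.

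Four stronger readings are tempting, and the document does not support them.

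- *The plan ignores baseline.* The article lists no covariates at all; it neither includes nor excludes the T0 score. A fuller protocol or analysis plan may list them. Nor does the article say item by item that the SF-36 is among the T0 questionnaires; the appendix that would show this is not at hand.
- *An unadjusted T1 comparison is biased.* Under randomization it is not, and its confidence interval already allows for chance imbalance at baseline.
- *The trial is underpowered at 64-78%.* Those figures hold only for Madrid alone at the largest SD, and the lower one only if the Madrid control arm is really 154.
- *The model will be chosen after seeing the data.* The text says nothing about when it will be built.

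**Conclusion.** The response variable of the effectiveness regression is wrongly defined in two places and should be corrected. That conclusion needs no assumption.

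Adjustment for T0 is a recommendation attached to the correction, because the sentence must be rewritten anyway. Its benefit is precision: the residual variance falls by the factor 1 − r², that is to 0.91, 0.75 or 0.51 of its unadjusted value at r of 0.3, 0.5 or 0.7. For Madrid as listed, at SD 27, this takes power for 6 points from 78% to 82-97%. At consortium size, or near SD 16, there is little left to gain. The range rests on the assumed correlation and alpha, and dropout and clustering by health center are ignored. It also depends on the SF-36 having been administered at T0 before allocation, which the text implies but does not state outright.

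**What to change.** Replace the sentence in the analysis section, and its counterpart in the abstract, with wording such as: *The dependent variable is each patient's SF-36 overall score at T1. It will be regressed on randomized group, adjusted for the T0 SF-36 score and for pathology, the factor by which patients are randomized. The effect is the adjusted mean difference between groups with its 95% CI.* The t test at T1 can stay as a descriptive comparison.

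First confirm that the SF-36 is in the T0 set. If it is not, drop that term; the correction to the response still stands. If a fuller protocol or analysis plan already specifies covariates, align the wording with it.

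The cost is a few sentences and no new data. The drawback is timing: recruitment began in April 2021 and the trial is unmasked, so this is a change to the primary analysis text after the start. It should be dated, recorded as such, and settled before the outcome data are analysed.

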## Methods

### Design

A multicenter, randomized, parallel-group clinical trial will be conducted with a follow-up of 2 months. The unit of randomization will be the patient.

This study protocol is part of a proposal with European funding under the European Union’s Horizon 2020 Research and Innovation Programme (grant 875325). The European consortium that developed the proposal is composed of different countries: Spain, Portugal, Italy, Slovenia, Greece, Germany, and Belgium [22].

The TeNDER project is developed in 4 European countries (Spain, Germany, Italy, and Slovenia). To account for the differences in the health systems of the participating countries and organizations, this research protocol refers to the primary care health centers (PCHCs) of the Madrid Health Service, which belongs to the Spanish public health system.

The TeNDER project brings together experts in technological development and users, including chronic patients, their caregivers, and primary care health professionals (PCHPs). Therefore, it will have an initial phase of cocreation in which the needs of the users will be explored. Based on the results, the technical team will work on improving and adapting the TeNDER system.

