### Recruitment

Five PCHCs in Madrid will be recruited. A total of 187 PCHPs will be invited to participate in the study. Based on experiences in previous studies, we expect a participation rate of 45%, which means 84 participating professionals. If necessary, the number of participating PCHCs will be expanded to reach the required sample size. PCHPs will participate in the study on a voluntary basis after signing the informed consent form.

Each participating PCHP will recruit 8 patients with a quota for each disease (5 with CVD, 1 with PD, and 2 with AD) consecutively as they attend the office. After the recruitment of patients, their caregivers will be invited to participate. For independent patients, it will not be necessary to recruit a caregiver.

During the recruitment interview, the PCHP will provide all information about the study as a detailed verbal explanation accompanied by a patient information sheet, making sure that the patient understands it.

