### Randomization

Once the participants have been selected, after the initial visit, the patients will be randomized by pathology. Patients included in the intervention group will be included together with their caregiver and PCHP, creating a participant unit (patient-caregiver-PCHP or patient-PCHP). There will be no masking in any phase of the study. Assignment will be performed centrally by the Research Support Unit of the Primary Care Management of Madrid.

Patients in the intervention group will be fitted with the TeNDER system device best suited to their needs and will be treated according to standard clinical practice. Patients in the control group will be treated according to standard clinical practice.

Subsequently, each PCHP will be informed of which patients have been assigned to each group; based on this, they will have a different role in each case (ie, using the TeNDER system with the intervention group and usual practice with the control group).

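### Robust estimators justified by clustering on PCHC most naturally rest on five clusters, which makes the standard error unstable and costs power in a patient-randomised trial

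*Protocol article*

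**What the plan says.** - **Variance method.** Under Data Analysis and Statistical Plan: "As patients will be recruited grouped by cluster (ie, PCHC), all the estimations will be performed with robust estimators". The rule covers every estimate, including the primary comparison of SF36 scores at 2 months. The abstract repeats the commitment to robust estimators.
- **Number of clusters.** Under Recruitment: "Five PCHCs in Madrid will be recruited". The same section allows more: "If necessary, the number of participating PCHCs will be expanded to reach the required sample size". It does not say how many.
- **Unit and manner of randomisation.** Under Design: "The unit of randomization will be the patient". Under Randomization: "after the initial visit, the patients will be randomized by pathology", with central assignment. Each professional is then told which of their patients are in which group.
- **A finer grouping.** Each professional (PCHP) recruits 8 patients. The expected participation rate of 45% among 187 invited is worked out as "which means 84 participating professionals".
- **Target and power.** Under Sample Size, the target is an SF36 improvement "of 6 points in the intervention group as compared to the control group". The SD ranges from 16 to 27, the highest value is used, and power of 98.8% is given for the consortium's 1766 patients. No power is given for Madrid, and no allowance for clustering appears.

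**The concern.** A cluster-robust (sandwich) variance is built from one residual total per cluster and is justified when there are many clusters. With five, the variance estimate carries about 4 degrees of freedom however many patients are enrolled.

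The design does not require this. Because patients are individually randomised, both arms are expected in each PCHC. A centre is then a block whose mean level can be removed with a centre term. The precision of the treatment effect can come from several hundred patients rather than from five centre totals.

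At stake are the power of the primary comparison and the width of its confidence interval, which could be far wider or narrower than the data warrant purely by chance.

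**Working it through.** **Inputs from the protocol article.** Difference 6 points; SD 27, with range 16 to 27; five PCHCs; two-sided testing. The 95% CI implies alpha 0.05 (assumption). The Madrid arms are given as 380 and 254, which sum to 634, while the stated total is 534. That conflict is a separate matter, so both 380/254 and 380/154 are used here.

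**Step 1: the plan's own figure.** Consortium, 735 versus 1031, SD 27:

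SE = 27 × √(1/735 + 1/1031) = 1.303; 6/1.303 = 4.60; power = Φ(4.60 − 1.96) = 99.6%.

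The article states 98.8%. The two agree to within a point, so the ingredients are understood.

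**Step 2: Madrid, ordinary two-sample comparison, SD 27.**

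- 380/254: SE = 27 × √(1/380 + 1/254) = 2.19; 6/2.19 = 2.74; power = Φ(2.74 − 1.96) = 78.3%.
- 380/154: SE = 27 × √(1/380 + 1/154) = 2.58; 6/2.58 = 2.33; power = Φ(2.33 − 1.96) = 64.3%.

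**Step 3: the same comparison with the variance clustered on five PCHCs.** The statistic is referred to t with 5 − 1 = 4 df (critical value 2.776). Power is taken from the non-central t with non-centrality 6/SE.

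| SD | Arms | Ordinary power | Five clusters, t(4) | Loss (points) |
|---|---|---|---|---|
| 27 | 380/254 | 78.3% | 54.7% | 23.6 |
| 27 | 380/154 | 64.3% | 42.7% | 21.6 |
| 20 | 380/254 | 95.9% | 78.8% | 17.1 |
| 20 | 380/154 | 88.1% | 65.7% | 22.4 |
| 16 | 380/254 | 99.6% | 92.5% | 7.1 |
| 16 | 380/154 | 97.5% | 83.1% | 14.5 |

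**Step 4: stability of the standard error.** With 4 df the ratio of estimated to true variance behaves roughly as χ²(4)/4. Its 5th and 95th percentiles are 0.178 and 2.372, with square roots 0.42 and 1.54. Around a true SE of 2.19 this gives about 0.9 to 3.4. The 95% CI width is 2 × 2.776 × SE, so 90% of widths fall between about 5 and 19 points. With an ordinary SE the width is about 2 × 1.96 × 2.19 = 8.6 points.

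**Step 5: type I error if 1.96 were used instead of 2.776.** P(|t(4)| > 1.96) = 12.2%.

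**Step 6: simulation check.** Individual randomisation 380/254 over five centres; ordinary least squares with the usual G/(G−1) × (N−1)/(N−k) correction. The centre ICC is not in the article; values of 0 to 0.05 were assumed and made little difference. Centres were equal, or unequal at an assumed 260/160/100/70/44.

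- Clustered on PCHC with t(4), SD 27: power 54-55% with equal centres and 59-60% with unequal centres. Type I error about 4-7%.
- The same SE with a normal reference: type I error about 11-15%.
- PCHC fixed effects, no clustering on PCHC: power about 78-80%, type I error about 5%.
- Loss at lower SD: 6-7 points at SD 16 and 14-18 at SD 20. The smaller loss in each pair comes from unequal centres.

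**Step 7: more centres.** With 10 PCHCs and t(9) at SD 27, power is 68.5% (380/254) or 54.6% (380/154). Type I error with 1.96 would be 8.2%.

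**The case against.** **The article says robust, not cluster-robust.** This stands as a caveat. If heteroscedasticity-robust errors were meant, neither harm arises: simulated type I error was about 5% and power matched the ordinary test. But the stated reason for the method is grouping by PCHC, and such errors would not address that grouping. The sentence needs correcting on either reading.

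**A reader might infer that the primary test will reject a true null too often.** The article does not support this. It names no reference distribution, and a journal article may leave that to the full plan. With t(4), type I error is near nominal and the intervals are roughly valid; they are inefficient and erratic in width. The 11-15% figure depends on a normal reference that nothing in the text specifies.

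**A reader might infer a loss of more than 20 points throughout.** For 380/254 that holds only near SD 27 with roughly equal centres. At SD 16 the clustered test still has 92.5% power.

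**Five centres is a plan, not a ceiling.** True, but expansion is conditional and unquantified, and at 10 centres the loss at SD 27 is still about 10 points.

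**The covariates are not listed, so a centre term may already be intended.** Possible, and its absence from the article is not the point. The point is the variance rule that the article does state.

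**Clustering on the professional is open to the same argument.** Largely right: professionals are also expected to have patients in both arms, and the 84 is a projection. It is therefore an option, not a requirement.

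**Conclusion.** The concern holds in a limited form. On its natural reading, the stated rule puts the standard error of the primary comparison on five clusters, and the randomisation does not call for this.

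Under t(4) the cost is power and stability, not validity. At the plan's own SD of 27, power falls from about 78-80% to 54-60% (380/254), or from about 64% to about 43% (380/154). Across the SD range of 16 to 27 with 380/254, the loss runs from about 6 to 24 points, depending on SD and on how evenly patients are spread over centres. Adding centres reduces the loss but does not remove it.

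The result rests on four assumptions: robust means clustered on PCHC; about five Madrid centres take part; alpha is 0.05; and the centre ICC lies between 0 and 0.05. It applies to Madrid only, because the number of centres in the wider consortium is not given.

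**What to change.** Replace the sentence on robust estimators with:

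*The primary model includes PCHC and the stratification factor, pathology, as fixed effects; standard errors are model-based or heteroscedasticity-robust and are not clustered on PCHC.*

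If dependence among patients of the same professional is a concern, cluster on the PCHP (about 84 expected) and refer the test to t with the number of clusters minus 1 degrees of freedom. A PCHP random intercept is an alternative, but it is a different estimator and not an equivalent.

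The change should be fixed before outcome data are examined. It costs one sentence and a few degrees of freedom: four for five centres, plus those for pathology. The PCHP option also requires the professional to be recorded for every patient, including controls, since the article describes the patient-caregiver-professional unit only for the intervention group.
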